#### Pilot study

A pilot study was conducted to refine and finalize the design (described in section “Intervention and control” below). The pilot was conducted in a randomly selected village that was not included in the main trial. A training session was provided at the start of the study on policy details and registration procedures in addition to financial incentives measures and benefits for village doctors to participate in the policy promotion (Additional file 5). Four village doctors working at the village clinic attended the training session. They then promoted the policy and assisted in registration for patients based on the intervention protocol. By the end of the study, telephone interviews were conducted with village doctors to learn details of the intervention implementation and their feedback on the intervention. During the intervention period of 1 week, the registration number of NCDs patients increased from 17 to 148. Village doctors also provided positive feedback on the training manual and policy promotion posters. Insights gained from the pilot study, such as overwhelming details of the intervention and the complicated registration procedures in DHCs, were used to modify and finalize the intervention.

### Trial overview

The intervention design was based on the results of the contextual research described in the previous section. PAPMed trial is an open-label cluster randomized controlled superiority trial with two parallel arms. The unit of the trial is a rural village served by a rural village clinic, which is an operational and administrative primary health clinic unit for providing NEPHS in China. All village clinics included in the trial are public-funding and non-profit institutions. Village doctors in the intervention village clinics will be main implementors of the intervention. They will promote policy, assist with registration, follow-up patients, and receive financial incentives based on their performance. Village doctors in the control group will not be contacted. The trial duration is 6 months. Figure 2 shows the trial flow chart.

**Fig. 2 Fig2:**
[figure not shown]
PAPMed trial flow chart

### Randomization

Thirty study villages in two townships will be included in the trial. Study villages will be randomly assigned to either the intervention or control arm with an allocation ratio of 1:1. Randomization will be stratified by township to minimize township confounding factors such as differences in DHCs healthcare services. Randomization is prepared a priori by a researcher at the coordinating center, independent of trial implementation. Within each township (strata), a random number sequence based on a random number seed was generated for each village in R (R Foundation for Statistical Computing, Vienna, Austria). The numbers were then sorted in increasing order, and the first half and second half villages were labeled “A” and “B,” respectively. Finally, a virtual coin flip was performed to assign one of “A” and “B” to the intervention and control arm. Allocation will be implemented by the research team, with DHCs in both townships enrolling intervention implementors based on the allocation results. The study will be conducted as an open-label trial as it is not possible to blind the intervention implementors and rural patients. Statisticians undertaking primary analyses will be blinded to allocation.

### Study population

#### Selection of intervention implementors

Village doctors at village clinics, as well as medical insurance staffs at DHCs, are implementors of the intervention. Village doctors who participated in the trial should meet all of the following inclusion criteria: (i) employed by the local government and registered in the village doctor management system annually; (ii) participate in NCDs management services; (iii) able to communicate with patients in Mandarin or local language. Village doctors meeting any of the following criteria are excluded from the trial: (i) worked in village clinics for less than 6 months at the start of the trial; (ii) aged 75 years old or above.

For each village, the village doctor responsible for NCDs management will be selected as the coordinator and organize the implementation of the intervention with all village doctors serving in the village clinic. Medical insurance staff at DHCs will be responsible for registering patients with approved applications into the registration system. All implementors will be informed and provided written consents before participation in the study and can withdraw from the study at any time.

#### Eligibility criteria and target populations

Hypertension or diabetes patients with RBHIS meeting any one of the following criteria are eligible for registration: (i) diagnosed with hypertension or diabetes by doctors at DHCs or above; (ii) regular usage of anti-hypertensive or anti-glycemic medications, with at least 3 times of hypertension or diabetes diagnoses and medication prescriptions in medical records; (iii) hypertension or diabetes patients recorded in CDMS and follow-up by village doctors more than once [20]. Hypertension or diabetes patients with urban employee health insurance or without RBHIS are not eligible for registration.

While all rural NCDs patients meeting the eligibility criteria are potential populations of the intervention, rural NCDs patients who are recorded in the hospital information system (about 90 to 95% of all rural NCDs patients) are selected as the main targets. The small proportion of patients not in the system will be included in the study but will not be actively recruited by village doctors due to feasibility concerns.

### Intervention and control

The intervention is a behavior science-based intervention program enabling village doctors to promote policy, assist registration, and enhance medication adherence, for patients. It is designed based on the principle of being simple, feasible, and scalable, with the potential to scale up to other rural settings with similar chronic disease reimbursement schemes nationwide. A summary of the intervention with targeted opportunities and barriers is shown in Table 2 and Table 3. In brief, identified opportunities and barriers were organized for changing a one-time target behavior of registering in the policy system, and a recurring target behavior of adopting policy to reimburse medical expenses, regarding predisposing, reinforcing, and enabling constructs in the PRECEDE-PROCEED model [47], at the stakeholder levels of NCDs patients, village doctors, and DHCs. Specific interventions were designed to target each of these opportunities and barriers at different levels, and systematically integrated as an intervention program in this trial.

#### Systematic training of village doctors

The research team provided systematic training for village doctors with training manuals drafted based on governmental documents and consultations with medical insurance officials, making adjustments to fit with the knowledge level and learning capabilities of village doctors (Additional file 5). Training will include project background, details of the policy and the registration procedures, measures of the performance-based financial incentives, benefits for village doctors to participate, and details of the intervention protocol.

#### Policy promotion and registration encouragement

(i) Policy promotion: Carefully designed picture-rich posters with examples of medical costs saved per patient and contact information of responsible village doctors will be hung out in villages. Locations will be selected by village doctors and officials in village committees based on the locations’ accessibility to villagers and ability to protect the posters. These include locations such as village clinics, village committees, village activity rooms, squares, and bus stations. Village doctors are encouraged to supplement the promotion through village broadcast, We-chat groups of NCDs patients, and one-on-one promotion to target populations. Village doctors will also encourage NCDs patients to inform the policy to other patients in the village to increase policy awareness and registration based on theory of peer effects [43].

(ii) Registration encouragement: Village doctors are required to encourage main target populations to register for the policy one-on-one based on standardized structure scripts, designed by the research team based on the theories of peer effects [43], reference point [44], and loss aversion [44].

#### Clearing up obstacles in the registration process

Multi-departmental coordination consisting of medical insurance officials in the city medical insurance bureau and DHCs, and representatives of village doctors in the intervention villages is led by the research team on streamlining the registration procedures prior to the intervention. Rights and responsibilities of collecting registration materials from patients, approving registration applications, and officially registering patients in the system are clarified. Experts on the medical insurance system one-on-one trained village doctors on system operation and solving software and hardware obstacles in village clinics.

#### Inform details of the policy to patients

Village doctors are required to inform policy details to patients after registration, including the reimbursement rate and applied designated medical institutions, and to encourage using the policy. Village doctors are also required to promote medication adherence by health education on NCDs comorbidities and regular intake of medications. Patients are encouraged to use the calendar in the flyers to keep records on medication intake and to ask family members to remind them. All communications will be based on standardized structure scripts, such as “XX, a chronic disease patient in the village like you, also participated in the project,” “The annual expense reimbursement is equivalent to you selling 300 kilograms of rice,” designed by the research team based on the theories of loss aversion [44] and encouragement [45].

#### Follow-up

Village doctors are required to follow-up on all registered patients in the first, third, and sixth months after baseline and are encouraged to integrate the follow-up into regular quarterly follow-up visits under NEPHS. Village doctors will monitor blood pressure and blood glucose, provide feedback, and repeat health education for patients. Village doctors will also encourage patients to adopt the policy and intake medications on time and in the right amount. All communications will be based on standardized structure scripts, designed by the research team based on the theory of positive feedback between motivation and behavior in the self-fulfilling prophecy [46].

#### Performance feedback and incentives

Village doctors’ performances will be evaluated based on timely real-world data of policy registration and adoption, provided by DHCs. The evaluation will take place after each time’s follow-up: village doctors will receive an appropriate amount of payment based on number of patients registered in the policy after the first month follow-up and will receive the same amount of payment based on number of patients purchasing medications with reimbursement provided by the policy during the follow-up period after the third and sixth month follow-up. Design of the performance-based financial incentives to change behavior is based on nudge theory [26, 31, 32].

#### Intervention implementation

The trial management committee will be responsible for trial implementation with the coordination of local governmental officials, and officials at DHC.Before intervention initiation, the research team within the trial management committee will clear up obstacles in the registration process through the multi-departmental coordination aforementioned;The research team will educate trial implementors on details of the informed consent, and written informed consent forms (Additional file 3) will be collected from all trial implementors who voluntarily agree to participate;The research team will inform village doctors of intervention protocol details through systematic training at baseline. Village doctors will then promote policy, encourage registration, and inform policy details to patients based on intervention protocol;Within 2 weeks after baseline, the research team will one-on-one conduct surveillance of each intervention village for 2–3 rounds. The purpose is to understand the intervention implementation conditions and clear up potential obstacles;During the first month and 3-month follow-up, the research team will evaluate policy registration conditions and communicate with the village doctors to remind policy promotion and informing policy details to patients;Throughout the trial implementation, the research team will establish an online instant communication We-chat group with trial implementors and provide feedback on policy registration and adoption conditions periodically, as well as provide performance-based incentive payment for trial implementors.

#### Control

Since the trial is designed as a superiority trial to test the effectiveness of the intervention program compared to usual practices, villages in the control arm will serve as a natural control and continue their usual practice without introduction of any intervention activities. To avoid contamination of the intervention activities, village doctors in the control villages will not be contacted and will not have access to any training sessions and materials correlated to the intervention. The streamlined registration process in DHCs will only be applicable to patients from the intervention villages. Although the likelihood is small, village doctors and patients in the intervention arm will also be asked not to discuss intervention-related contents with their counterparts in the control arm. We did not anticipate and define relevant concomitant interventions that are permitted or prohibited during the trial.

### Outcome measurements

The primary outcome of the trial is the policy registration rate of NCDs patients recorded in CDMS. Information of NCDs patients registered in the policy will be collected and matched with CDMS at baseline, 3-month, and 6-month follow-up. Policy registration rate will be calculated as the proportion of NCDs patients registered in the policy in CDMS. The effectiveness of the intervention program will be evaluated by the policy registration rate between the intervention and the control arm. Secondary outcomes include the following:Total number of policy registrations including those that are not recorded in the hospital information system, collected at baseline and 6-month follow-up;Total hypertension and diabetes medication costs during duration of follow-up, collected at 6-month follow-up;Frequency of village doctor visits during duration of follow-up, collected at 6-month follow-up;Blood pressure level, including systolic blood pressure and diastolic blood pressure, measured with blood pressure monitor, if available from electronic health records or government-funded annual physical examination records;Blood glucose level, measured by blood tests, if available.

Data collection will rely on existing real-world administrative data (mainly insurance claims data) to reduce cost and increase study feasibility.

After the end of the follow-up period, we will also collect qualitative data through in-depth individual interviews of about six village doctors, ten patients, and several government officials and policymakers. Such data will provide insight on intervention fidelity, differential effects from different intervention components, and other feedback. We will conduct post-trial assessments relying on data collection from real-world administrative data periodically, to evaluate the longer-term effects of the intervention program. We will attempt dissemination of effectiveness of the intervention program through various channels, including policy forums or other forms with local healthcare officials. The trial schedule of procedures from beginning to end is shown in Fig. 3 below.

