**Methods:**

Barriers and opportunities affecting stakeholders in adopting the policy were identified through contextual research and summarized through behavior mapping. The intervention is designed to target these barriers and opportunities through behavior science theories and will be evaluated through a 6-month cluster randomized controlled trial in Tongzhou District, Nantong, China. A total of 30 villages from two townships are randomized in a 1:1 ratio to either the intervention or the control arm (usual practices). Village doctors in the intervention arm (1) receive systematic training on policy details, registration procedures, and intervention protocol, (2) promote the policy and encourage registration, (3) follow up with patients in the first, third, and sixth months after the intervention, and (4) receive financial incentives based on performance. The primary outcome is policy registration rate and the secondary outcomes include the number of patients registering for the policy, medical costs saved, frequency of village doctor visits, and health measures such as blood pressure and glucose levels.

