### Study site

This study is being conducted in Tongzhou District, which is a district with high NCDs burden. According to a health census report based on medical examination data of regional health records of 125,769 participants aged over 65, the overall prevalence of hypertension and type 2 diabetes were 53.8% and 12.1%, while the control rates were 41.0% and 47.0%, respectively in 2017 [35]. Despite rapid urbanization in the past decade, a large socioeconomic gap remains between rural and urban residents of the district. In 2019, the annual disposable income of rural residents was 25,846 RMB (about 4011 United States Dollars (USD)), less than half of that of urban residents in Tongzhou district [36].

Tongzhou transferred from a rural county to an urban district in 2009 with a large proportion of the residents remaining rural. Rural areas are consisted of 12 townships, with 205 villages under these townships [37]. Two townships were selected to take part in this study based on the selection criteria of having (i) a typical representation of the socioeconomic development of rural areas of Tongzhou District, (ii) with village clinics serving 400 NCDs patients or more per year; (iii) available village doctors who can be trained to implement the intervention, and (iv) support from local healthcare institutions and township leaders. Majority of the residents in these two townships are under rural *hukou* (Chinese household registration system).

The local healthcare infrastructure is consistent with the primary healthcare system of rural China, characterized by a hierarchical system of county hospitals, district health centers (DHCs), THCs, and village clinics [38]. DHCs are secondary-level hospitals responsible for diagnosing and treating NCDs patients. There is one village clinic in each village with 3 to 7 village doctors carrying out regular quarterly follow-up visits on NCDs patients under the NEPHS program, mainly including monitoring blood pressure and blood glucose, health education, and medication consultation.

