### Analysis plan

The principle of intention-to-treat will be adopted in our analysis, where we will analyze clusters and patients as they have been randomized, regardless of the intervention they have received [50]. Individual patient data will be grouped by cluster and condensed to cluster level data. Summary analyses will be performed on a cluster level. Categorical variables will be reported as counts and proportions. Continuous variables will be reported as mean and standard deviation if symmetric or median with 25th and 75th percentile if skewed. Variables between the intervention and the control group will be compared, with *t*-test performed on continuous data and *χ*^2^ test performed on categorical data, and *P* value less than 0.05 is considered as statistically significant.

Effectiveness of the intervention on primary and secondary outcomes will be estimated with marginal modeling using generalized estimating equations (GEEs) to account for stratification and clustering [51, 52]. Robust variance estimation will be used to provide valid standard errors and to account for potential model misspecification [53, 54]. The modified Poisson approach with a log link will be used to obtain risk ratios for estimates of intervention effect with binary outcomes [53]. Main analyses will include adjustments for stratification and cluster effect. Baseline covariates will be cross-tabulated by randomization arm to check for substantial imbalance by chance. Additional analysis will be performed that will additionally adjust for identified imbalance baseline covariates. Potential effect measure modifiers impacting the effectiveness of the intervention program will be evaluated by stratified analysis. Imputation for missing data is not planned in main analyses since there is no reason to assume data is not missing at random. However, if we identify baseline covariates that are predictive of missingness, we will adjust for these covariates in additional analysis or implement multilevel multiple imputations to test for sensitivity of missing data on the results. For each outcome, we plan to report the estimate of intervention effect and its 95% confidence interval (CI), as well as estimate of intra-cluster correlation coefficients (ICCs) and its 95% CI.

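### The first secondary outcome is a raw count of registrations with no denominator, so differences in village size add noise to the arm comparison and blur its meaning

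*Protocol article*

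**What the plan says.** All references are to the Protocol article.

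- **The outcome.** The Outcome measurements section lists as the first secondary outcome "Total number of policy registrations including those that are not recorded in the hospital information system, collected at baseline and 6-month follow-up". The abstract agrees: "secondary outcomes include the number of patients registering for the policy". Both describe a number of people, not a rate.
- **The primary outcome, for contrast.** In the same section: "Policy registration rate will be calculated as the proportion of NCDs patients registered in the policy in CDMS". This one has a denominator.
- **Randomization.** "Study villages will be randomly assigned to either the intervention or control arm with an allocation ratio of 1:1". The only stratification factor is township: "Randomization will be stratified by township to minimize township confounding factors such as differences in DHCs healthcare services".
- **Main analysis.** The Analysis plan condenses patient data to village level and estimates effects on primary and secondary outcomes by GEE with robust variance. On adjustment it says: "Main analyses will include adjustments for stratification and cluster effect". The modified Poisson model with a log link is specified for binary outcomes.
- **Further adjustment.** "Additional analysis will be performed that will additionally adjust for identified imbalance baseline covariates". Village size is not named there.
- **Village size.** No distribution is given. The Study site section says: "There is one village clinic in each village with 3 to 7 village doctors".

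**The concern.** A larger village yields more registrations at any given registration rate. With 15 villages per arm, no stratification by size and no size term in the stated main analysis, the ratio of arm totals is the product of two things: the ratio of registration rates, which is of interest, and the ratio of arm populations, which is an accident of the draw. A reader of the result cannot separate them. Between-village variation in size also enters the standard error, so the same data are less informative as counts than per listed patient.

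The outcome has a purpose the primary does not serve, because it captures registrants outside the hospital system. At stake are how precisely and how clearly that one secondary result can be read.

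**Working it through.** **Inputs.** From Statistical power: 5250 patients, 15 villages per arm, ICC 0.04, two-sided alpha 0.05, difference 8.5 percentage points, baseline registration below 10%. I read 5250 as per arm, so the mean village size is m = 5250/15 = 350. The village-size CV is not in the document. If doctors per clinic (3 to 7) were spread evenly, their CV would be 0.28, but doctors are only a proxy for patients. I therefore use 0.2 to 0.5.

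**Step 1: the plan's own figure, for the primary outcome.** Design effect = 1 + (350 - 1) × 0.04 = 14.96. Effective n per arm = 5250/14.96 = 350.9. Power for an 8.5-point difference (pooled normal) is 97.4% from a 5% control rate, 94.7% from 7% and 89.8% from 10%. The claim of more than 90% therefore reproduces for control rates below 10%. No power is claimed for the count.

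**Step 2: chance imbalance in arm size.** Count ratio = rate ratio × population ratio. The SD of the log population ratio is about CV × √(2/15) = 0.365 × CV. The 95% chance range is exp(±1.96 × SD):

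| CV | SD of log ratio | 95% range of population ratio |
|---|---|---|
| 0.2 | 0.073 | 0.87 to 1.15 |
| 0.3 | 0.110 | 0.81 to 1.24 |
| 0.4 | 0.146 | 0.75 to 1.33 |
| 0.5 | 0.183 | 0.70 to 1.43 |

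**Step 3: lost precision.** Per village, in units of m, the variance of a count is

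V(p) = p²CV² + p(1 - p)[ICC(1 + CV²) + (1 - ICC)/m].

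At CV = 0.4:
- V(0.10) = 0.0016 + 0.09 × (0.0464 + 0.00274) = 0.00602.
- V(0.185) = 0.00548 + 0.1508 × (0.0464 + 0.00274) = 0.01289.
- SE = √[(0.00602 + 0.01289)/15] = 0.0355, and 0.085/0.0355 = 2.39, so normal power is about 67%.

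For rates, taking every village at the mean size:
- Variances are 0.09 × 0.04274 = 0.00385 and 0.1508 × 0.04274 = 0.00644.
- SE = √[(0.00385 + 0.00644)/15] = 0.0262, and 0.085/0.0262 = 3.24, so normal power is about 90%, or 88% with a t reference on 28 degrees of freedom.

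**Step 4: simulation.** Gamma village sizes, beta-binomial registration, t-test on 15 vs 15 village values, 20,000 trials per setting:

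| CV | Counts, 10% vs 18.5% | Rates | Counts, 7% vs 15.5% | Rates |
|---|---|---|---|---|
| 0.2 | 83% | 88% | 90% | 93% |
| 0.3 | 76% | 88% | 86% | 94% |
| 0.4 | 67% | 88% | 79% | 93% |
| 0.5 | 57% | 88% | 72% | 93% |

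If 5250 is the total for both arms (m = 175), count power runs from 81% to 56% and from 89% to 71%, with rates at about 85-86% and 92%. The conclusion does not depend on that reading.

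**Step 5: validity.** With equal rates in both arms, the t-test on counts rejects in about 4% to 5% of trials across these CVs. Under 10% vs 18.5%, the ratio of arm totals falls below 1 in about 0.1% of trials at CV 0.2 and about 1.2% at CV 0.5.

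**The case against.** **Detail left to the analysis plan.** A condensed article gives the link only for binary outcomes, and an offset for the count may stand in a document not shown. This has some force. But the outcome itself is defined as a total, next to a primary outcome defined as a proportion, and the adjustment set of the main analysis is stated. Followed as written, size stays in.

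**A scaled version already exists.** The primary outcome is nearly the same quantity as a proportion and covers about 90-95% of patients, and no exact denominator exists for the rest. This stands, and it limits the point to a supplementary outcome. It does not make the total easier to interpret.

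**A safeguard exists.** Baseline covariates are checked for imbalance and adjusted for in an additional analysis, and the count is also collected at baseline. Size could enter there, but it is not named and the step is conditional. With 12% and 2% registered in the two townships at the time of the interviews, the baseline count is a weak proxy for size.

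**The power figures may be harsh.** A 10% control rate is the edge of what the protocol states, a t-test on raw counts stands in for the GEE, and the 8.5-point difference belongs to the primary. This stands. A t-test on log counts, a crude stand-in for a log link, gives 81%, 74% and 66% at 10% vs 18.5% for CV 0.3, 0.4 and 0.5. At 10% vs 25%, raw counts give 99%, 96% and 91%. The clinic selection criterion of 400 or more patients a year may also limit size variation.

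**Stronger readings that the document does not support.**
- A reader might infer bias or false positives. Randomization makes size imbalance zero on average, and type I error does not exceed 5%.
- A reader might infer that the count will often contradict the primary. At the design difference, reversal by chance occurs in about 1% of trials or fewer.
- A reader might infer that registrants outside the system will be credited to whichever clinic registers them. No such rule is stated. The Analysis plan analyses patients as randomized, and the Control section restricts the streamlined process to patients from intervention villages, which implies that residence is identified at registration.

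**Conclusion.** The point holds as one of precision and interpretation for a single secondary outcome. As defined, and with the main analysis as stated, the count carries village size into the arm comparison. The chance range of the arm population ratio is about 0.87-1.15 at CV 0.2 and 0.70-1.43 at CV 0.5. Across that range the power cost is about 5 to 31 percentage points at 10% vs 18.5%, and about 3 to 21 at 7% vs 15.5%.

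These sizes rest on an assumed village-size CV, on 15 villages per arm averaging 350 patients with ICC 0.04, and on a village-level t-test in place of the planned GEE. A larger intervention effect or more even villages would shrink the cost. The primary outcome and its power statement are not touched.

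**What to change.** In the Analysis plan, specify that the main analysis of total registrations models the village count by GEE with a log link, robust variance, the township term and an offset of log(village size). Village size should be fixed before randomization, for example the baseline CDMS patient count. In Outcome measurements, add that the result is reported as registrations per 100 listed patients, beside the raw total.

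The cost is one sentence in the outcome definition and one model term. CDMS is already needed for the primary denominator, so no new patient data are required.

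The downside is that the CDMS list omits the 5-10% of patients outside the system, while the numerator includes any of them who register. Registrations per 100 listed patients is therefore a scaled count, not a true proportion. It should be labelled that way, but the denominator is fixed at baseline and defined identically in both arms.
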